## Abstract

**Background:**

Evidence on the effectiveness of low-cost, sustainable, biological vector-control tools for the *Aedes* mosquitoes is limited. Therefore, the purpose of this trial is to estimate the impact of guppy fish (guppies), in combination with the use of the larvicide pyriproxyfen (Sumilarv® 2MR), and Communication for Behavioral Impact (COMBI) activities to reduce entomological indices in Cambodia.

**Methods/design:**

In this cluster randomized controlled, superiority trial, 30 clusters comprising one or more villages each (with approximately 170 households) will be allocated, in a 1:1:1 ratio, to receive either (1) three interventions (guppies, Sumilarv® 2MR, and COMBI activities), (2) two interventions (guppies and COMBI activities), or (3) control (standard vector control). Households will be invited to participate, and entomology surveys among 40 randomly selected households per cluster will be carried out quarterly. The primary outcome will be the population density of adult female *Aedes* mosquitoes (i.e., number per house) trapped using adult resting collections. Secondary outcome measures will include the House Index, Container Index, Breteau Index, Pupae Per House, Pupae Per Person, mosquito infection rate, guppy fish coverage, Sumilarv® 2MR coverage, and percentage of respondents with knowledge about *Aedes* mosquitoes causing dengue. In the primary analysis, adult female *Aedes* density and mosquito infection rates will be aggregated over follow-up time points to give a single rate per cluster. This will be analyzed by negative binomial regression, yielding density ratios.

**Discussion:**

This trial is expected to provide robust estimates of the intervention effect. A rigorous evaluation of these vector-control interventions is vital to developing an evidence-based dengue control strategy and to help direct government resources.

**Trial registration:**

Current Controlled Trials, ID: ISRCTN85307778. Registered on 25 October 2015.

**Electronic supplementary material:**

The online version of this article (doi:10.1186/s13063-017-2105-2) contains supplementary material, which is available to authorized users.

## Background

Dengue is one of the most rapidly spreading mosquito-borne viral diseases in the world, and is caused by bites of infected *Aedes* mosquitoes, principally *Aedes aegypti* [1]. Dengue infection is a systemic and dynamic disease with a wide clinical spectrum that includes both severe and non-severe manifestations and in some cases can lead to death [1]. With an estimated 3.6 billion people in 124 countries at risk of contracting the disease [2] and 390 million dengue infections occurring each year (of which 96 million are clinically apparent) [3], the dengue virus has become a leading cause of illness in the tropics and subtropics [4]. Asia records 70% of the global disease burden due to dengue [3] and Cambodia has one of the highest per-capita incidence rates in the region [5].

Identified in Cambodia in 1963 [6], a total of 194,726 dengue cases were reported to the National Dengue Control Program (NDCP) between 1980 and 2008 [7]. Between 2003 and 2008, annual dengue incidence ranged between 0.7 and 3.0 per 1000 persons, the cost to society estimated at between US$3,327,284 and US$14,429,513 [8]. Since most of this cost falls onto the family, it is estimated that 67% of affected households (HHs) fall into debt to pay for medical bills [9]. However, it is likely that the real number of cases and cost to society is much greater, with some studies suggesting the real case numbers are between 3.9 and 29.0 times higher than those of the National Dengue Surveillance System [10, 11].

Although a number of promising vaccine candidates are in preclinical and clinical development [12], and methods of genetic control of mosquitoes are being developed [13–15], they are years from operational roll-out in Cambodia and are unlikely to provide universal protection. Without a cure or vaccine the most appropriate dengue control measures are vector control and the avoidance of mosquito bites. Several vector-control methods have been studied in Cambodia including chemical and biological substances (temephos, pyriproxyfen (PPF), and *Bacillus thuringiensis israelensis* (*Bti*)) [16–19], jar covers [20], and distribution of larvivorous copepods and fish [21–23].

### Past research

*Ae. aegypti* is highly anthropophilic (preference for human beings), endophilic (resting indoors), and endophagic (preference for feeding indoors) [19]. This partially explains why previous studies showed that household water storage jars contained over 80% of *Ae. aegypti* larvae in Cambodia, and why these jars became the main target for dengue vector-control activities [20]. Since the early 1990s, the NDCP has used the larvicide temephos (distributed with brand name Abate®) to target large (200–400 L) household water containers as the primary means of vector control [19]. This has continued despite susceptibility tests in 2001 showing resistance of *Ae.* a*egypti* in urban Phnom Penh and incipient resistance in a rural province in Cambodia [24]. An evaluation of the effectiveness of temephos control programs to control larvae in 2007 concluded that control strategies emphasizing the use of temephos should be reconsidered [19]. Although temephos was only distributed during the rainy season, there were still containers found to be positive for immature *Aedes* during the dry season; and the program ignored discarded containers – which had twice the number of larvae as water storage containers. Khun and Manderson (2007) concluded that “continued reliance on temephos creates financial and technical problems, while its inappropriate distribution raises the possibility of larvicide resistance [19].”

Following the success of *Mesocyclops* (a genus of copepod crustaceans) programs in locally eliminating *Aedes* mosquitoes in Vietnam [25–27], the Cambodian NDCP implemented a 2-year *Mesocyclops* project in Kratie province from 2002 to 2004, searching for an alternative vector-control option [23]. Initial results showed a reduction in the *Aedes* population in the intervention area, but by the end of the project larval densities in the intervention area had increased by 62% from baseline. This apparently lower effectiveness in Cambodia may be because *Mesocyclops* from the local water sources had various parasites, and colonizing them parasite-free requires special training beyond what is possible in most rural Cambodian villages. The environment could have played a role as Northern Vietnam (where programs were most successful) has four distinct seasons and has different flora and fauna. Additionally, many people did not accept *Mesocyclops* to the same extent as other interventions that were provided by the NDCP such as temephos (personal communication, [name], 2015).

The search for other vector-control options continued with an evaluation of *Bacillus thuringiensis israelensis* (*Bti*), a Gram-positive, soil-dwelling bacterium used as a biological control agent [18]. The evaluation of *Bti* in Phnom Penh showed positive results with significant reductions in the number of pupae for at least 2 and 2.5 months in containers with river and well-water, respectively [18]. More extensive usage and evaluation of *Bti* by the Cambodian government are currently occurring in Kandal and Kampong Thom Provinces (personal communication, [name], 2015).

Jar covers with long-lasting insecticidal netting (LN) treated with deltamethrin were found to have significantly fewer pupae per house, a three-fold decline in *Ae. aegypti* adult females per house and adult mosquito survival [20]. However, the magnitude of the reduction diminished over time due to a gradual reduction of insecticidal effect of the jar covers and a residual deltamethrin life of 22 weeks [20]. Interestingly, this is less than the average residual life of deltamethrin in treated bed nets [21]. Another cause may have been children not always keeping the jar covering on after extracting water, and using the covers as toys around the house (personal communication [name], 2015) as Khun et al. noted in Cambodia before [28]. Improvements in engineering and design to prevent entry and egress of mosquitoes, especially when the container is used, and an increase the insecticidal effectiveness may be needed for jar covers to be cost-effective public health interventions [20].

The use of a larvivorous guppy fish (guppies) (*Poecilia reticulata*) was evaluated in 14 Cambodian villages [21], and subsequently in a larger study of 28 Cambodian villages [22]. Results from the initial study done from 2006 to 2007 were extremely encouraging with guppies in 56% of eligible containers, and a 79% reduction in *Aedes* infestation compared to the control. Guppy fish are not able to colonize all potential *Aedes* breeding sites, especially those which are polluted or with volume of less than 50 L (personal communication [name], 2015). However, despite not having guppies, the smaller or discarded containers in the intervention villages had 51% less infestation than those in the control, suggesting a community-wide protective effect [21]. This could partly be due to a spillover effect from treatment villages as no results of guppy coverage were reported in the paper. These results led the World Health Organization (WHO) and the Asian Development Bank (ADB) to fund a larger scale-up in 2010–2011 which included Communication for Behavioral Impact (COMBI) activities. Results showed 88% guppy fish coverage in eligible water containers and a Container Index (CI), i.e., proportion of surveyed containers containing *Ae. aegypti* larvae/pupae and indoor resting adult females of near 0 (while the control had a CI of 30) at the end of the project [22]. Similarly encouraging results were found in Laos as a part of the same project. However, there were additional miscellaneous breeding sites including containers too small for guppy survival. Additional tools beyond larvivorous fish are required to target these varied, hard-to-reach and cryptic breeding containers or sites.

One such alternative that has been evaluated in Cambodia is pyriproxyfen (PPF) [16, 17]. PPF is a juvenile hormone analog that interferes with the metamorphosis of juvenile *Aedes* mosquitoes, preventing their development into adults [29]. The results of the first study in 2003 were so promising – at higher doses, inhibition of adult emergence (IE) greater than 87% for 6 months – that a larger second study was designed [16]. This showed that a novel 5% controlled-release formation led to IE above 90% for 20 weeks, and above 80% for 34 weeks [17]. A slow-release PPF matrix release formulation (Sumilarv® 2MR) has since been developed and is suitable for containers uninhabitable by guppy fish. The added benefit of this product is that it only requires one distribution every 6 months (the entirety of the rainy season) and cuts down on operational costs as compared to temephos or *Bti* which have a residual efficacy of 2–3 months [18, 30].

The effective implementation of Integrated Vector Management requires mobilization and coordination of the resources needed to achieve and sustain behavior changes among populations at risk of dengue [31]. The COMBI strategy provides a social mobilization and communication approach that connects knowledge and behavior, addresses the cost and value of engaging in healthy behaviors, recognizes the gradual stages of behavior change, and creates a supportive environment for behavior change [32]. The challenge for vector control is how community participation can be integrated into vector breeding-source reduction efforts [22]. Community health workers (CHWs) are a vital part of successful COMBI communication and social mobilization activities. A recent review of 22 studies found that educational messages embedded in a community-based vector-control approach were effective at reducing *Ae. aegypti* measured through entomological indices [33]. A separate systematic review found that community-based control strategies in addition or together with biological and chemical vector-control tools reduced classical *Aedes* larval indices in five of six field trials [34]. Two cluster randomized trials published after the reviews showed that a community empowerment strategy embedded in a routine dengue vector-control program drastically reduced entomological indices [35, 36]. These past studies show the importance of having a strong community-based COMBI strategy, and the important contribution that it can add when integrated into the vector management strategy.

### Need for a trial

Although there is evidence suggesting that the use of guppy fish can be beneficial in dengue vector control, recent reviews show that there has never been a cluster randomized trial to evaluate their effectiveness to reduce mosquito indices [37]. Although some studies have evaluated the use of community-based communication programs for dengue control, a recent review found that none had assessed their costs [34]. This trial has the potential to inform the strategic application of community-based distribution of PPF and larvivorous fish in an outbreak, during inter-epidemic periods or for broad-scale application. This trial will also be the first to our knowledge to evaluate the wide-scale use of the new Sumilarv® 2MR product in the field (personal communication, [name], 2015). Although guppies, PPF, and COMBI activities have all been evaluated, some of these evaluations were methodologically flawed. Furthermore, they have never been tested in combination. Therefore, our study is intended to fill the knowledge gaps identified above.

### Hypothesis

This trial aims to demonstrate community effectiveness of guppies, PPF, and COMBI activities. The main hypotheses are:Use of guppies, Sumilarv® 2MR, and COMBI activities will reduce numbers of *Aedes* mosquitoes, and their infection rates, more than guppies and COMBI alone, or usual Ministry of Health activities (including larval control and information and education material dissemination during outbreaks) as assessed through entomology surveysCOMBI activities will improve the community’s knowledge, attitudes, and behavior around water use and vector-borne disease prevention (such as burning or burying discarded containers, cleaning the environment around the house, and sleeping under a bed net) as assessed through baseline/endline surveys and Focus Group Discussions (FGDs)Guppies and PPF will be acceptable among the target villages as assessed by an endline survey and FGDs

The study is designed as a cluster randomized controlled, superiority trial with three parallel arms.

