#### Sample size

The guppy fish and PPF interventions will be assessed by an entomology survey. A sample size of 10 clusters per arm and 40 HHs per cluster for the survey was devised using the Hemming and Marsh method [45]. The calculation assumed a mean of 0.1 adult female resting *Aedes* mosquitoes per HH in the intervention arms compared to 0.25 in the control arm for each collection. This assumption was based on the results from the earlier World Health Organization/Asian Development Bank guppy fish project in the same province [22], and to be conservative assumed no impact from the PPF in arm 1. The HHs will be randomly selected at each collection. The intracluster correlation (ICC) was assumed to be 0.01 based on previous studies [46–48]. Additionally, a sensitivity analysis was conducted up to the median value of ICCs for outcome variables (0.03) as found by an analysis conducted by Campbell et al. [49]. Our analysis determined that we would have between 91 to 75% power at ICC values between 0.01 to 0.03. The coefficient of variation in cluster sample size was assumed to be 0.1, and is expected be small as we plan to sample the same number of houses from each cluster. Under these assumptions the study will have 91–75% power to detect a difference at the 5% significance level.

COMBI activities will be evaluated through Knowledge, Attitudes, and Practice (KAP) surveys. A sample size of 10 clusters per arm and 20 HHs per cluster was devised, again using the Hemming and Marsh method [45]. The calculation assumed a 22.5% change in primary outcome indicators from 40 to 62.5% in intervention villages and no change in the control villages over the course of 1 year. Outcome indicators include:Percentage of respondents with knowledge about *Aedes* mosquitoes causing denguePercentage of HHs that keep guppy fish/PPF in water

This calculation was based on the results from the earlier projects done by Malaria Consortium (MC) in the region, and a recent unpublished MC KAP survey completed in six provinces and 30 villages in 2014. The ICC was assumed to be 0.01, and the coefficient of variation of cluster size assumed to be 0.1. Under these assumptions the study will have 90% power to detect a difference at the 5% significance level.

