### Entomology

A baseline survey was conducted prior to start of interventions. An endline survey will be conducted 1 year after the baseline. Two additional surveys during the dry season (4 months post intervention) and light rain (8 months post intervention – peak dengue season) will also be conducted. The schedule of the surveys took into account data from the previous guppy fish project [22]. The survey methodology was developed following the WHO guidelines for entomological collections [1]. Surveys will include indoor adult resting catches and larvae/pupae collection from water containers. The survey team consisted of experienced government staff who received 3 days’ training before beginning. All tools and materials were pre-tested during training. The same team will be used for each entomology survey. Houses within each cluster were selected using a random-number generator [50] applied to the village list managed by the village head.

The adult resting catch will be completed using a battery-powered, portable aspirator (Camtech, Phnom Penh, Cambodia) for 10 min per house in the bedrooms and living spaces, starting in the bedroom and aspirating up and down the wall (from floor to 1.5 m) around the home in a clockwise manner. The mosquitoes will be kept in a screw-top containers inside a cold box and transported to the provincial laboratory for identification to the species level for *Aedes*, otherwise to genus. All *Aedes* mosquitoes will be sexed. After identification they will be stored in a −20 °C freezer and taken to the United States Naval Medical Research Unit 2 (NAMRU-2) in Phnom Penh for confirmation. All *Aedes* females will be pooled and subjected to flavivirus rRT-PCR screening [51]. Flavivirus-positive pools will be further tested for dengue typing by semi-nested RT-PCR assay targeting the C and pre-M regions within the viral genome [52].

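### Mosquito infection rate is ranked inconsistently (main hypothesis and primary analysis in two places, secondary elsewhere), no power is shown for it, and the stated model would mix it with density

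*Protocol article*

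**What the plan says.** The protocol article gives the infection rate different ranks in different places.

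- **Hypothesis.** The first main hypothesis is that guppies, Sumilarv 2MR and COMBI together will reduce *Aedes* numbers "and their infection rates, more than guppies and COMBI alone, or usual Ministry of Health activities". Infection is therefore claimed against both arm 2 and control.
- **Abstract, Methods/design.** "In the primary analysis, adult female *Aedes* density and mosquito infection rates will be aggregated over follow-up time points", and negative binomial regression is then said to give density ratios.
- **Primary outcome measures**, and **Primary outcome** under Statistical methods. Both cover adult female density only.
- **Secondary outcome measures**, and **Secondary outcomes** under Statistical methods. Infection is listed as secondary, to be analysed by the methods given for density: negative binomial regression with the logarithm of aspirating person-time as offset.

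The Sample size section works on density alone: "A sample size of 10 clusters per arm and 40 HHs per cluster for the survey". On the densities it says: "The calculation assumed a mean of 0.1 adult female resting *Aedes* mosquitoes per HH in the intervention arms compared to 0.25 in the control arm". These figures apply at every survey round. It adds that the investigators "to be conservative assumed no impact from the PPF in arm 1". It gives no infection prevalence, effect size or power. In the Entomology section, the mosquitoes tested for virus are those caught in the surveys: "All *Aedes* females will be pooled and subjected to flavivirus rRT-PCR screening".

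**The concern.** Two things are at stake. The first is what the trial will claim. If infection belongs to the main hypothesis and the primary analysis, it is a headline result. If it is secondary, it is supporting evidence. The article supports both readings, and the choice should be settled before follow-up results are seen.

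The second is what an infection result could mean. The number of females tested is a by-product of a density survey, and the intervention arms are expected to catch fewer. A comparison with little power that carries main-hypothesis status invites a non-significant result to be read as no effect on virus in the vector. The opposite error is also possible. With effort as the offset, a significant ratio could come entirely from catching fewer mosquitoes and still be reported as a lower infection rate.

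**Working it through.** **Plan's own figure.** There is none for infection. The only stated power is 91–75% for density at ICC 0.01–0.03. It cannot be reproduced from the stated inputs because no standard deviation is given. With design effect 1 + ((0.1² + 1) × 40 − 1) × ICC = 1.394 and 2.182, a common SD of about 0.515 (t, 18 df) returns both ends, so they agree with each other. That figure is not in dispute here.

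**Step 1: females available.** The inputs are 10 clusters per arm, 40 houses per cluster and densities of 0.25 and 0.1 per house per collection (Sample size), with follow-ups at 4, 8 and 12 months (Data collection methods).

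- House-collections per arm: 10 × 40 × 3 = 1,200
- Control: 1,200 × 0.25 = 300 females
- Each intervention arm: 1,200 × 0.1 = 120 females

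The Abstract calls the surveys quarterly. Four follow-ups would give 400 and 160, which does not change the conclusion. Any real effect of pyriproxyfen would lower the arm 1 catch further.

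**Step 2: power for infection as a proportion.** The documents give no infection rate, so the control rate *r* is an assumption. This is a best case: each mosquito is tested individually, there is no clustering, and the test is Fisher exact at two-sided 5%, 300 versus 120. Expected positives are 300*r* in control and 120 × *r*/2 = 60*r* after a halving.

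| Control rate *r* (assumed) | Expected positives, control / halved | Power, halving | Power, 75% reduction | Power, elimination |
|---|---|---|---|---|
| 0.5% | 1.5 / 0.3 | <1% | <1% | <1% |
| 1% | 3 / 0.6 | <1% | <1% | <1% |
| 2% | 6 / 1.2 | 1–2% | 2% | 4% |
| 5% | 15 / 3 | 15% | 39% | 89% |
| 10% | 30 / 6 | 33% | 79% | >99% |

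By normal approximation, 80% power for a halving needs a control rate of about 23%. With 0/120 positive in an intervention arm, control needs at least 11/300 (3.7%) positive for p ≤ 0.05. Zero of 120 leaves an upper two-sided 95% limit of 1 − 0.025^(1/120) = 3.0%. Arm 1 versus arm 2 is weaker: 120 versus 120, with a 5% rate in arm 2, has about 9% power for a halving. Clustering and pooled testing would be expected to lower all of these.

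**Step 3: what the stated model estimates.** Effort is fixed by design at 10 minutes per house and the same number of houses per arm. Infected females per unit effort equal density × prevalence, so

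ratio = (0.1 / 0.25) × (prevalence ratio) = 0.4 × (prevalence ratio).

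If prevalence is unchanged, the ratio is 0.4; if it is halved, 0.2. At *r* = 5% with unchanged prevalence, expected infected females are 300 × 0.05 = 15 versus 120 × 0.05 = 6 for the same effort. An exact conditional Poisson test of those means is significant at two-sided 5% about 42% of the time. On this reading, an apparent reduction in infection rate can arise with no change in the share of mosquitoes infected.

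**The case against.** The strongest reply is that the methods sections have already settled the rank. Outcome measures and Statistical methods both make density alone primary and infection secondary, and secondary outcomes are commonly unpowered. That stands: the absence of a power figure for a secondary outcome is no error in itself. It does not remove the conflict with the Hypothesis section and the Abstract.

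A second reply is that the Fisher figures do not test the analysis described. Taken literally, the plan compares infected females per unit effort, where a smaller catch is part of the effect. For a halved prevalence (300*r* versus 60*r* expected positives, exact conditional Poisson test, same best case), power is then 0.3%, 5%, 28% and 79% at *r* = 0.5%, 1%, 2% and 5%. This is fair, and infected-female density is a legitimate quantity. It is not, however, a result separate from density, and the hypothesis names infection rates alongside numbers. Much of the higher power comes from the density difference.

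Third, the Discussion already concedes that the study was not powered between the intervention arms. That stands for arm 1 versus arm 2. No similar limit is stated for infection against control.

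A reader might go further and infer that the infection question cannot be answered, or that the result will be null whatever the truth. The documents do not support this. They give neither an infection rate nor an effect size, and the table in the working shows adequate best-case power at some combinations. Nor does the article say that a null would be read as no effect; that risk comes from the rank given to the outcome.

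**Conclusion.** The point holds as a problem of rank, interpretation and estimand. The article gives infection main-hypothesis and primary-analysis status in two places and secondary status elsewhere. The counts of about 300 and 120 per intervention arm follow from its own assumptions. Best-case power for a halved infection proportion is about 0–15% over an assumed control rate of 0.5–5%, so the comparison is badly underpowered unless infection is common or the effect very large. Separately, the effort offset lets the planned density effect alone produce a ratio of about 0.4.

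The power conclusion rests on the assumed infection range and effect size, on three follow-ups and on the planned densities. The inconsistency in rank and the estimand problem do not depend on the infection rate. The change is worth making because it is cheap and settles what the trial claims. It does not call the primary density analysis into question.

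**What to change.** Three changes, all in wording and analysis:

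1. Remove infection rates from the first main hypothesis and from the primary-analysis sentence in the Abstract. Keep infection as a secondary, descriptive outcome, in line with the outcome measures.
2. Under Secondary outcomes in Statistical methods, exempt infection from the effort-offset model. Report positive pools, pool sizes and a pooled-prevalence estimate with an exact interval for each arm. If infected females per unit effort is also wanted, report it under that name.
3. State that the absence of a difference in infection will not be interpreted as absence of effect.

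The same mosquitoes are tested in the same way, provided pool sizes are recorded and pools stay within arm. The cost is one fewer headline claim.
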